### Methods to improve study adherence

The exercise intervention was based on the Theory of Planned Behavior
[50], which is a motivational theory of human behavior. Various behavior change techniques were incorporated into the intervention to increase intentions to exercise (i.e., motivation to do the exercise program), planning for exercise (i.e., detailed plans for the exercise program), instrumental attitudes (i.e., anticipated benefits of the exercise program), affective attitudes (i.e., anticipated enjoyment of the exercise program), injunctive norm (i.e., perceived approval and social support for the exercise program), descriptive norm (i.e., perceived role modeling of the exercise program), and perceived behavioral control (i.e., perceived controllability and self-efficacy for doing the exercise program).

#### Start Up package, incentives and feedback

Since the participants were inactive when they enrolled in the study, a start up package with various items needed to begin a regular exercise program was provided to each participant. The package included: a voucher for a new pair of running shoes, a water bottle, an athletic t-shirt and a journal to document their weekly activities and progress. Other incentives, such as gift certificates (obtained through donations), were given to participants as they reached various milestones throughout the trial. Participants were provided with continuous feedback on their progress from the exercise trainers and were given a summary and explanation of results from all fitness and anthropometric assessments that were taken at the beginning and end of the study.

#### Educational and group sessions

The exercise trainers facilitated monthly hour-long group exercise sessions for participants. These sessions were an opportunity for participants to learn new aerobic activities and interact with other participants. Educational sessions also instructed participants on various topics related to overall health and wellness, e.g., injury prevention, learn to run, stretching and flexibility. Sessions were not mandatory but participants were encouraged to attend.

#### Adherence challenges

Adherence challenges were used to improve compliance during periods when attendance was expected to be lower than normal, such as the summer months and winter holidays. During these challenges, participants with perfect or near perfect compliance were eligible to win various prizes e.g., gift certificates, donations from local merchants, to acknowledge their commitment to the study.

#### Parking expenses

To ensure participants did not incur additional expenses while participating in the study, any parking costs associated with study-related appointments were reimbursed.

#### Vacation planning

Our exercise trainers met with the participants before planned vacations and completed a *Vacation Planning Form* that included strategies for maintaining exercise whilst away. Since each participant had her own heart rate monitor, they were asked to continue wearing the monitor and maintaining their weekly exercise logs for the duration of their vacation. These materials were returned to study staff at the end of the vacation.

#### Absences and illness

Participants were expected to plan their weekly supervised sessions and to book these with our exercise trainers who followed up by telephone and email with any participants who missed their supervised sessions. Reasons for absences were recorded and a central communication book was maintained so that all exercise trainers knew the status of each participant at all times. If a participant was ill and unable to exercise, the exercise trainers worked with them individually to help them resume their exercise program once they returned to regular sessions.

#### Newsletters and website

To maintain contact with our study participants, we created a quarterly newsletter that was mailed or emailed to all participants directly. It included updates on the study progress, profiles of study participants from each center, study staff profiles, as well as general articles on health topics. We also created and maintained an active study website (
http://www.beta-trial.com) that was used extensively for communication and information dissemination with the study participants. Finally, we produced a cookbook with recipes from study participants and staff that was professionally printed and distributed as a gift and souvenir of the research study to all the participants. Collectively, all of these activities increased the sense of attachment and interest in the study.

#### Social events

To maintain engagement and permit social interaction between the participants, exercise trainers and study staff, several social events were organized that included two formal events held at the universities in each centre, as well as events either at the recreational centre or another location off-site. These events included presentations from the study principal investigators on the study progress and from the exercise trainers on tips for maintaining motivation and interest. In addition, some events included guest speakers, booths by local cancer charities and fitness companies, door prizes, activities to increase awareness and contact between participants as well as fundraisers for local cancer charities. Teams of study participants were also created who trained together and walked in fundraising events for these cancer charities. When all women had completed the 12-month intervention in June 2013, wrap up events were held in each centre to provide an overview of the study for all participants and to encourage them to maintain their current activity levels. Participants who achieved 100% adherence throughout the trial were also recognized at these events.

#### Post-intervention resistance exercise training

The exercise intervention in the BETA Trial was restricted to aerobic exercise only. In response to the expressed interests of our study participants, we developed a short one-day resistance exercise training educational session with accompanying reading materials. Once the participants had completed all of their 12-month tests and assessments, they were free to attend one of these sessions led by one of our exercise trainers in each center. The purpose was to introduce the main principles and components of resistance exercise training. There was no requirement to attend and no additional follow-up provided.

#### Data collection and measurements

A complete data collection schedule is provided in Table 
3. All assessments, except the PARmed-X and baseline health questionnaire, were completed in the baseline phase, at the end of the 12-month exercise intervention, and again at 24 months to assess exercise maintenance.

**Table 3 Tab3:** **Data collection schedule for the BETA Trial, Alberta, Canada**

Assessments	Time (months)			
	−1 to 0 baseline*	6	12 end of study	24 follow-up
**Early screening**				
Participant Eligibility Questionnaire	x			
**Questionnaires**				
Baseline Health	x			
Past Year Total Physical Activity Questionnaire	x		x	x
Canadian Diet History Questionnaire	x		x	x
Quality of Life	x		x	x
Predictors of Exercise Adherence	x		x	x
Psychological Stress	x		x	x
Satisfaction with Life, Happiness	x		x	x
Sedentary Behavior (SIT-Q)	x		x	x
Pittsburgh Sleep Quality Index	x		x	x
Participant Satisfaction with Exercise Intervention			x	
**PAR Med-X** ^**1**^	x			
**Objective measurements**				
Blood Sample	x	x	x	x
Submaximal Fitness Test	x		x	x
Anthropometry (height, weight, waist/hip circumference)	x		x	x
Accelerometry	*x* ^2^	x	x	x
CT Scan^3^	x		x	x
DXA Scan^4^	x		x	x

*All baseline measurements and questionnaires were completed prior to randomization. The exercise intervention began at baseline (time 0).

^1^PAR Med-X: Physical Activity Readiness Medical Examination.

^2^Step count data were retrieved from the accelerometer devices to assess study eligibility for any participant with a VO_2max_ determined to be between 34.6 and 37.0 mL/kg/min.

^3^CT Scan: Computed Tomography Scan.

^4^DXA Scan: Dual Energy X-Ray Absorptiometry Scan.

#### Questionnaires

##### Baseline health

Baseline health characteristics and other demographic information were collected through a self-administered questionnaire that we developed and used previously. Questions were asked regarding marital status, education, employment as well as medical, menstrual and reproductive history. Additional questions addressed history of vitamin, medication and exogenous hormone use.

##### Physical activity and sedentary behavior

Physical activity in the previous 12 months was self-reported at baseline and at 12 and 24 months post-randomization using the *Past Year Total Physical Activity Questionnaire* (*PYTPAQ*)
[51]. This questionnaire, developed by our study team, measures all types of occupational, household and recreational physical activity and transportation to perform work as well as the duration, frequency and intensity of these activities. The questionnaire has been shown to have acceptable reliability and validity
[51]. All reported activities are coded and converted into MET-hours/week/year using the *Compendium of Physical Activities* developed by Ainsworth and colleagues
[52–54]. This measure of total physical activity, which includes activities performed outside the intervention, will be used to characterize our study population.

Similarly, participants were asked at baseline and 12 months to report how much time they spent in sedentary activities over the past year using a sedentary behavior questionnaire called the *SIT-Q*. This questionnaire was developed just prior to the BETA Trial by one of our study investigators ([name]) and has since undergone psychometric testing and shown to be a reliable and valid tool for sedentary behaviour assessment
[55]. Given that sedentary behavior has been linked to many of the same breast cancer biomarkers as physical activity
[56, 57], we will explore in our analyses how sedentary behaviour changes with our exercise intervention.

##### Dietary habits

Dietary intake for the previous 12 months was reported at baseline and at 12 and 24 months using the self-administered Canadian version of the US National Cancer Institute’s *Diet History Questionnaire*[58]. Study participants were asked not to change their dietary intake during the study. Hence, we are interested in verifying if dietary intake was changed since the primary purpose of this study is to examine the independent effect of physical activity on breast cancer biomarkers. In addition, given that energy intake impacts body weight, and because dietary composition might impact proposed biomarkers of risk
[59–62], diet will be considered as a potential confounder (although the randomization reduces the chances of this) in our statistical analyses.

#### Blood data

A 60 mL blood sample was taken at baseline after a minimum 10 hour fast and complete abstinence from exercise and alcohol for 24 hours. From the 60 mL, 20 mL were used for eligibility screening to assess for underlying medical conditions that would preclude participation. Screening tests included a complete blood count, lipid panel, fasting glucose, creatinine, alanine aminotransferase and thyroid stimulating hormone. Each was required to be within normal reference ranges for the participant to be eligible for the study. If the woman was under 55 years of age and had not had a bilateral oophorectomy or was uncertain of her menopausal status, a follicle stimulating hormone test was also done. The additional 40 mL of blood from the baseline blood draw was saved for analysis of endogenous sex and metabolic hormones and other biomarkers. At baseline, if the participant did not begin the exercise intervention within eight weeks of the initial blood test, a repeat 40 mL, non-screening blood draw was required to ensure true baseline values of the various biomarkers being examined. Additional 40 mL blood samples were taken at six, 12 and 24 months. A complete blood collection, processing, shipping and storage protocol was developed for this study to ensure standardization of procedures at both collection sites. All blood samples are stored in −86°C freezers in the Alberta Cancer Research Biorepository in Calgary. Freezerworks® Unlimited software (version 6.02) was used to track and manage the location and quantity of all collected samples.

Estradiol and estrone will be measured by radioimmunoassay with preceding organic solvent extraction and Celite column partition chromatography steps. The assay sensitivities are 2 pg/ml and 4 pg/ml, respectively, and the interassay coefficients of variation (CVs) are 9-14%. SHBG, insulin and high sensitivity CRP will be measured by solid-phase, two-site chemiluminescent immunometric assays on the Immulite analyzer (Siemens Healthcare Diagnostics, Deerfield, IL). The assay sensitivities are 1 nmol/L, 2 μIU/ml, and 0.02 mg/dL, respectively, and the interassay CVs are <10%. Glucose will be quantified by a standard analytical procedure using the Vitros Chemistry System. Ten additional biomarkers (from our original study aims and hypothesized post-study funding) will be quantified using three different multiplex assays: the Human Adipokine panel, the Human Circulating Cancer panel and the Human High Sensitivity panel according to the manufacturer’s protocol (Millipore, St. Charles, MO, USA). The assays will be performed at Eve Technologies (Calgary, AB, Canada) using the Bio-Plex™ 200 system (Bio-Rad Laboratories, Inc., Hercules, CA, USA). The Human Adipokine panel assesses adiponectin and resistin with assay sensitivities ranging from 2.2-11 pg/mL, the Human Circulating Cancer panel contains leptin, FGF2, prolactin and VEGF with sensitivities ranging from 3.6-42.8 pg/mL, and the Human High Sensitivity panel contains IL-4, IL-6, IL-10 and TNF-α; with sensitivities ranging from 0.11-1.12 pg/mL. Appropriate quality control samples will be used to monitor the reliability of each assay. Blood samples are batched so that each participant’s baseline, six and 12 month samples are in the same batch and an equal number of MODERATE and HIGH exercise volume bloods are in the same batch. Blind duplicates are included in and between batches to estimate coefficients of variation. All assays will be repeated for the 24-month blood samples. All lab personnel will be blinded to the intervention assignment.

#### Health-related fitness assessments

Only participants who successfully passed the baseline blood screening criteria were invited for health-related fitness assessments (Figure 
1) that included resting heart rate and blood pressure assessment, a submaximal fitness test, anthropometric and body composition measurements. All fitness assessments were performed by a Canadian Society for Exercise Physiology Certified Exercise Physiologist (CSEP:CEP®) and one assistant exercise trainer. The same testing protocols and equipment were used at the Edmonton and Calgary study centers and all measurements were taken at baseline and at 12 and 24 months.

##### Resting heart rate and blood pressure

Following standard procedures
[63] participants were instructed to sit quietly for five minutes before measurements were taken. Heart rate was monitored using a Polar FT4 heart rate monitor (^©^Polar Electro, Canada). Resting blood pressure was measured using a sphygmomanometer (WelchAllyn®) and stethoscope (3 M™ Littmann®). A blood pressure reading of 144/94 mmHg or lower was required for the participant to undergo the fitness test.

##### Body composition/Anthropometry

Anthropometric data on standing height, weight, waist and hip circumference were measured using standardized methods and equipment at the time of the fitness tests. Waist circumference was measured using the National Institutes of Health protocol and hip circumference was measured using the World Health Organization procedure with an anthropometric measuring tape
[64]. Full body dual energy X-ray absorptiometry (DXA) scans were taken using a Hologic DXA system in Calgary and a General Electric Lunar iDXA in Edmonton to assess overall percent body fat, total lean body mass, total fat mass and bone mineral density. Computed tomography (CT) scans were taken at the level of the umbilicus to measure subcutaneous and intra-abdominal adiposity. Three single slices were taken at the L5 vertebrae and these data were then transferred to our study radiologist at the Cross Cancer Institute in Edmonton who reviewed each scan individually using a software program (Aquarius Intuition by Terarecon, Inc.) that was used to quantify amount of subcutaneous and intra-abdominal fat at this level of the abdomen. Because of the high cost associated with both the DXA and CT scans, only participants who had completed all screening stages and considered eligible for the study were given these scans at baseline. These assessments were repeated 12 months and 24 months later (Table 
3).

##### Cardiorespiratory fitness

All participants completed a sub-maximal cardiorespiratory testing to assess their aerobic fitness and determine eligibility (Table 
1; Figure 
1). The multistage, modified Balke treadmill test protocol was used
[65] in which a speed of 3.0 mph is maintained throughout the test and the grade is gradually increased every three minutes by 2.5% starting at 0%. The test was completed when the participant finished the stage in which she reached 85% of her age predicted maximum heart rate or reached volitional exhaustion. The participant’s predicted VO_2_ max was estimated using the multistage model and the American College of Sports Medicine metabolic equations for estimating maximum oxygen consumption
[66]. To be eligible for the BETA Trial, a minimum of two stages of the test had to be completed and estimated VO_2_ max had to be ≤ 34.5 mL/kg/min (Table 
1). If the estimated VO_2_ max was between 34.6 mL/kg/min and 37 mL/kg/min, additional assessments of their activity levels were needed. In these individuals additional step count data were retrieved from the accelerometer devices (Actigraph GT3X + ® and *activPAL™*) that all participants were required to wear for seven days. If it was determined that, on average, these participants walked <10,000 steps/day they were eligible for the study. Any woman with an estimated VO_2_max greater than 37 mL/kg/min was ineligible for the study. A modified version of the fitness test was repeated at 3, 6, and 9 months post-randomization for external verification of reported adherence to the exercise prescription and as a means to adjust the prescription. Randomization into the study occurred after all health related fitness tests were completed including the DXA and CT scans (Figure 
1).

#### Objective measurements of physical activity and sedentary behaviour

An accelerometer and inclinometer were worn by participants at four time points during the trial - baseline, six, 12 and 24 months (Table 
3) - to complement self-reported physical activity and sedentary behavior in the *PYTPAQ* and *SIT-Q*, respectively. The ActiGraph GT3X + ® accelerometer (Actigraph, LLC, Pensacola, FL) was used to assess moderate-vigorous physical activity since the GT3X+ model is particularly suitable for measuring upright moderate-vigorous intensity movement. The accelerometers were worn on the hip and recorded the duration, frequency and intensity of movement. The *activPAL™* inclinometer (PAL Technologies Ltd, Glasgow, Scotland) was adhered to the upper thigh area. This device measured duration and frequency of time spent sitting, standing and stepping (light ambulation), and number of postural changes. The *activPAL™* inclinometer is considered the most accurate device for assessing sedentary time in adults
[67]. All participants were asked to wear both devices simultaneously for seven days immediately after their fitness tests. As mentioned above, the step counts on the Actigraph GT3X + ® were also used to determine eligibility in any woman with an estimated VO_2max_ that was deemed potentially too high. Additionally, they were required to record, in a daily activity log, when the devices were worn each day and which activities they were doing when not wearing the device, e.g., showering or swimming since only non-sleep activity was recorded.

#### Participant-reported outcomes

Participants completed self-administered questionnaires at baseline, 12 months, and 24 months to assess quality of life, sleep quality, perceived stress, satisfaction with life, and happiness; psychosocial factors that have been associated with exercise in some intervention trials
[23, 44–46] and observational studies
[68, 69] and therefore might improve with increasing exercise dose. Quality of life was measured using the *RAND SF-36*[70] which includes 36 questions and uses eight subscales to assess physical and social functioning, pain, mental health. Questions were also asked about stress using the *Perceived Stress Scale*[71] and sleep using the *Pittsburgh Sleep Quality index*[72]. Happiness and satisfaction with life were assessed using the Happiness Measure
[73] and the Satisfaction with Life Scale
[74], respectively.

#### Determinants of physical activity

The social cognitive determinants of physical activity were assessed at baseline, 12 months, and 24 months through participant-administered questionnaires that followed the standard questions based on the Theory of Planned Behavior
[50]. This theory assesses attitude, subjective norm, perceived behavioral control, intentions and planning. At the end of the study, the participants were also asked to complete a *Participant Satisfaction Questionnaire* to assess their attitudes and barriers towards exercise.

#### 24-month follow-Up

An earlier follow-up of ALPHA Trial participants, on average 12 months post-study completion, demonstrated that a high follow-up response rate was attainable; however, this follow-up was restricted to completion of one self-administered questionnaire pertaining to exercise maintenance. In the BETA Trial, 24-month assessments included all questionnaires, the blood draw, fitness tests, anthropometric and body composition assessments and objective measures of physical activity and sedentary behaviour.

### Sample size

Sample size calculations were based on a standard two-sample mean comparison formula using α = 0.05 (two-sided). Taking a conservative approach, the means of 12-month outcomes (log-transformed, with adjustment for baseline values) were compared. Results from the ALPHA Trial provided estimates of standard deviations and ‘yardstick’ intervention effects that might be expected. A sample size of 150 participants/group was chosen, providing 80% power to detect anticipated changes of 12% in insulin resistance and inflammatory outcomes (leptin, insulin, adiponectin) at 12 months and 99% power to detect changes as low as 2% in all body fat outcomes. While an initial group size of 165 was planned, because of more rapid recruitment than anticipated due to tremendous participant interest in the study, we increased the sample size to 400 per group without incurring extra resource requirements. The increase in sample size created a slight improvement in power, on average, and adequately accounted for an anticipated 10% loss-to-follow up and more modest exercise adherence that we postulated might occur with the higher demands associated with the exercise intervention in the HIGH volume arm of the trial.

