[7] of case–control and/or cohort studies. However, observational studies alone cannot inform public health guidelines due to their inherent limitations (e.g., inconsistent definitions of physical activity, physical activity measurement error, and possible confounding by other factors). A more definitive understanding of the dose–response relation can be gained using a randomized controlled trial (RCT) study design.

In the Alberta Physical Activity and Breast Cancer Prevention (ALPHA) Trial
[19], we examined how a 12-month aerobic exercise prescription, compared with a usual inactive lifestyle, influenced hypothesized biologic mechanisms for breast cancer risk in 320 postmenopausal women in Alberta, Canada. The exercise group was prescribed 225 minutes/week of moderate-vigorous physical activity, five days a week, with at least half of each workout reaching 70-80% heart rate reserve. Among women assigned to the exercise arm (n = 160), we observed a strong effect of exercise on the main proposed biomarkers of interest that included an effect on endogenous estrogens, insulin resistance, inflammation and body composition
[19–22]. In addition, we observed favorable dose–response relations across subgroups of exercise adherence (minutes/week) with respect to 12-month changes in body weight, total body fat, and intra-abdominal fat area
[20], circulating free estradiol and sex hormone-binding globulin (SHBG) levels
[19], insulin and the homeostasis model assessment of insulin resistance (HOMA-IR), leptin, adiponectin:leptin
[21] and high sensitivity C-reactive protein (CRP), with the strongest changes occurring when exercise exceeded 150 or 225 minutes/week. Dose–response relations were not found for androgens
[19], tumor necrosis factor-alpha (TNF-α) or interleukin-6 (IL-6)
[22]. Furthermore, greater improvements in quality of life variables were observed with exercise duration over 150 minutes/week (p-trend < 0.05 for seven of eight quality of life variables)
[23]. Two comparable trials in postmenopausal women
[10, 24] observed similar effects of an exercise intervention on hypothesized breast cancer biomarkers as well as some suggestion of a dose–response effect with stronger improvements in some biomarkers when exercise exceeded 195 minutes/week
[24–26] or 130 minutes/week
[12, 27] but not with others

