Evolving from the ALPHA Trial, the **B**reast Cancer and **E**xercise **T**rial in **A**lberta (BETA) Trial was conducted in Alberta, Canada between 2010 and 2014. The primary objective was to compare the effects of a high versus moderate volume of aerobic exercise on proposed biologic intermediate endpoints for breast cancer in previously inactive, postmenopausal women. We hypothesized that 300 minutes/week of moderate to vigorous intensity aerobic exercise would induce stronger changes in proposed breast cancer biomarker levels than would 150 minutes/week, the minimum weekly volume that is currently recommended for cancer prevention. Our specific hypotheses were that the higher volume exercise intervention would decrease adiposity levels (body mass index (BMI) (weight (kg)/height (m^2^)), percent body fat, subcutaneous and intra-abdominal fat) and circulating levels of endogenous estrogens (estradiol, estrone, SHBG), insulin resistance indicators (insulin, glucose, leptin, adiponectin), and inflammatory markers (TNF-α, IL-6, high sensitivity CRP) in a dose–response manner compared to the moderate volume exercise intervention. Secondary aims were to evaluate the impact of the intervention on quality of life, perceived stress, happiness, satisfaction with life, sleep quality, exercise adherence, and exercise maintenance 12 months after study completion, and to identify predictors of exercise maintenance. Although we
[23, 42, 43] and others
[44–46] have assessed these secondary outcomes in previous exercise trials, very few
[41, 47] were designed to identify dose–response effects. In addition, we aimed to evaluate the long-term benefit of a higher volume exercise intervention on proposed biomarkers for breast cancer 12 months after study completion. The primary intent of the BETA Trial is to determine whether a higher volume of aerobic exercise is likely to provide further reductions in breast cancer risk compared to the current moderate volume recommendations. Such information will inform public health guidelines addressing how to lower postmenopausal breast cancer risk through physical activity.

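### The added women cover at most about a 9% dilution of the blood-marker effect, and the power claimed for inflammatory outcomes covers none of the protocol's inflammatory markers

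*Protocol article*

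**What the plan says.** The Sample size section uses a "standard two-sample mean comparison formula using α = 0.05 (two-sided"), applied to log-transformed 12-month outcomes adjusted for baseline. The size first settled on is 150 women per group, which the section describes as "providing 80% power to detect anticipated changes of 12% in insulin resistance and inflammatory outcomes (leptin, insulin, adiponectin) at 12 months"; the same size is said to give 99% power for a 2% change in body fat outcomes. "Results from the ALPHA Trial provided estimates of standard deviations" and the yardstick effects; the article prints no SD.

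The section first planned 165 per group and then, in its own words, raised this to 400 per group. It credits the increase with a slight average gain in power, and says it "adequately accounted for an anticipated 10% loss-to-follow up and more modest exercise adherence that we postulated might occur" under the heavier demands of the HIGH arm. It gives no expected level of adherence and no dilution of effect.

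The Abstract, Trial overview and Statistical methods all give 400 women in total, and the last gives this as the number randomized. The Background lists "insulin resistance indicators (insulin, glucose, leptin, adiponectin") as one class of biomarker, and TNF-α, IL-6 and high sensitivity CRP as the separate inflammatory class.

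**The concern.** Two statements in the power paragraph claim more than its figures carry.

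First, the same added women are credited with a gain in power, with covering loss to follow-up, and with covering weaker adherence in the HIGH arm. The analysis is by intention to treat, so any adherence shortfall stays in the estimated difference. The comparison is between two exercising arms prescribed 300 and 150 min/week, so a shortfall confined to the HIGH arm comes straight off a 150-minute contrast.

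Second, a reader of the power sentence would take inflammation to be a powered pathway, when no marker in the protocol's own inflammatory class is named there.

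Both bear on how a null result for the blood markers is read. The Discussion presents the trial as central to deciding whether 300 min/week is better than 150. A null finding would be weighed against the power stated here.

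**Working it through.** **Inputs, all from the protocol article.** Two-sided α = 0.05; 150 evaluable per group; 80% power for 12%; 99% power for 2% in body fat; 10% loss (Sample size). 400 randomized in total (Statistical methods), in two arms balanced in number (Randomization), so 200 per group. 300 versus 150 min/week (Interventions). 96% retention (Discussion).

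**1. The plan's own figures.** With no SD printed, the 150 cannot be checked independently. It can be back-solved: SD = δ × √(150/2) / (1.960 + 0.842).
- 12% increase: δ = ln 1.12 = 0.1133, so SD = 0.350.
- 12% decrease: δ = −ln 0.88 = 0.1278, so SD = 0.395.

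The planned 165 is 150 × 1.10. Dividing instead, 150/0.90 gives 167. With 165 per group, 10% loss leaves 148.5 and 79.6% power. The initial plan therefore covered the loss and nothing more. Any allowance for adherence must come from the enlargement.

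**2. Which group size.** Taken literally, 400 per group leaves 360 after loss. That would give 99.1% power and tolerate 1 − √(150/360) = 35% dilution. It contradicts the 400 randomized in total, and a rise from 80% to 99% is not slight. The figures below use 200 per group.

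**3. What 180 evaluable per group delivers.** 200 × 0.90 = 180. With f the fraction of the 12% effect (log scale) that remains:

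power = Φ(2.802 × √(180/150) × f − 1.960) = Φ(3.069 f − 1.960)

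| Dilution (1 − f) | Power at 180 per group |
|---|---|
| 0% | 86.6% |
| 5% | 83.0% |
| 8.7% | 80.0% |
| 10% | 78.9% |
| 15% | 74.2% |
| 20% | 69.0% |

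The break-even is 1 − √(150/180) = 1 − 0.913 = 8.7%. It does not depend on the SD, the effect or the power level. The noncentral t distribution gives 8.8%. At 96% retention (192 per group) the break-even is 1 − √(150/192) = 11.6%.

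The gain to 86.6% and the 8.7% allowance both come from the same 30 extra evaluable women per group. They can be shared, as in the 5% row, but not both counted in full.

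**4. What this means in minutes.** Assume that effect is proportional to the difference in minutes and that the MODERATE arm averages 150.
- The allowance is used up when HIGH averages 150 + 150 × 0.913 = 287 of 300 min/week.
- At 270 (90% of prescription), f = (270 − 150)/150 = 0.80 and power is 69%.
- If instead both arms reach 90%, f = (270 − 135)/150 = 0.90 and power is 79%.

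**5. Body fat outcomes.** For 99% power the multiplier is 1.960 + 2.326 = 4.286. At 180 per group it becomes 4.286 × √1.2 = 4.695. Power falls to 80% only when f = 2.802/4.695 = 0.597, a dilution of about 40%.

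**6. Marker classes side by side.**

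| Marker | Class in Background hypotheses | Named in the 80% power claim |
|---|---|---|
| Insulin, leptin, adiponectin | Insulin resistance | Yes |
| Glucose | Insulin resistance | No |
| TNF-α, IL-6, CRP | Inflammatory | No |
| Estradiol, estrone, SHBG | Estrogens | No |

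**The case against.** The strongest reply is that the adequacy claim is not shown to be wrong. The article fixes no adherence level, a dilution under 8.7% would be covered, and a condensed article may leave the adherence assumption and per-marker power to a fuller document. That stands: the missing detail is not itself a fault, and the absence of a power figure for the estrogens is not an error. What the article does print is a positive claim of adequacy, next to a group size that conflicts with its own total.

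The proportional-dose illustration is also open to challenge. The Background reports the strongest changes in the predecessor trial above 150 or 225 min/week, which may not be linear. The minutes in step 4 are therefore illustrative; the 8.7% does not rely on them.

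A further reply is that the pathway-based multivariate analysis is the primary one, so single-marker power does not describe it directly. That is true, but single-marker power is what the section states.

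On the label, the parenthesis shows which markers were meant, so a careful reader is not misled. That limits the harm without making the word inflammatory correct.

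A reader might infer more: that the 12% is the predecessor's effect for its whole contrast ("The exercise group was prescribed 225 minutes/week of moderate-vigorous physical activity" against usual inactivity) and must be scaled down for 300 versus 150, or that the inflammatory markers are too variable to be powered at all. The documents support neither. They do not say how the 12% was derived. The Discussion reports that 53% of the predecessor's controls began exercising, and its effects may already include non-adherence. No SD is given for any marker.

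**Conclusion.** Both parts hold, with limits.

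(1) On 400 women in total and 10% loss, the enlarged sample keeps 80% power for the blood markers only up to an 8.7% dilution of the 12% effect (11.6% at 96% retention). The claim that it adequately covers weaker adherence is unsupported beyond that small margin. It is not proven false. The margin rests on the article's own figures, with equal arms and the normal approximation. The readings of 287 and 270 min/week also need proportional effect and full adherence in the MODERATE arm.

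(2) By the Background's own classes, the stated 80% power covers no inflammatory marker.

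A reader might conclude that the trial as a whole is underpowered. That does not follow. Power is 86.6% without dilution and about 79% if both arms reach 90% of prescription, and body fat outcomes keep 80% power up to about 40% dilution. The fault lies in how power is reported, and it matters for reading a null blood-marker result.

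**What to change.** - Correct 400 per group to 400 in total, 200 per group.
- Replace the adequacy claim with what the numbers show: after 10% loss, 180 evaluable women per group keep 80% power for about an 11% difference, that is, at most about 9% dilution of the 12% effect. Check: 0.913 × 0.1133 = 0.1034, which is a 10.9% increase; 0.913 × 0.1278 = 0.1167, which is an 11.0% decrease.
- Limit the 80% statement to leptin, insulin and adiponectin as insulin resistance markers. Alternatively, give detectable differences for TNF-α, IL-6, CRP and the estrogens at 180 to 200 per group, from the predecessor trial's SDs.

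No participants or new data are needed, since the article says that the predecessor trial supplied SD estimates. The cost is that the stated power becomes slightly less favourable.
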